### Sample size

Of the 59 villages in the Nouna HDSS, 25 were randomly selected (or about half of all the villages in the Nouna HDSS area), generating a total of 50 strata. We randomly selected 12 homes in each village with mud brick roofs and 12 with tin roofs. We randomized these homes (*n* = 600) in each category (1:1) to either the intervention (cool roof application) or the control condition (no cool roof application). The distribution of these 600 households across the trial groups was evenly balanced between mud brick and tin roof houses and between the intervention and control groups. Each of the 600 households enrolled in the study included one female and one male participant (*n* = 1200 participants).

### Power calculations

Prior non-randomized studies indicate that reducing the indoor temperature by 3–4 °C should decrease heart rate by several beats per minute [32, 50, 51]. Because of high uncertainty about the previous findings, their attributability to the climate and context in rural Burkina Faso, and the relatively large number of secondary endpoints, our cRCT is powered conservatively (Table 3). In the baseline power calculation, the minimal detectable heart rate difference between the cool roof intervention and control condition arm is 0.22 beats per minute (Table 3) for 300 homes (in the intent to treat) in both arms, assuming a significance level of 5% and power of 80%. We further assumed that 15% of homes refuse to participate in the trial and 15% of individuals would be lost to follow-up. Our sensitivity analyses showed that these power calculation results are highly robust to changes in intra-cluster correlation, the number of individuals in which the outcomes were measured per home, and the base correlation generated by our stratification (Table 3).

**Table 3 Tab3:** Minimal detectable difference in heart rate — baseline power calculation and sensitivity analyses

No. individuals/baseline correlation	1	2	3
ICC = 0.1			
0	0.28	0.21	0.18
0.1	0.28	0.21	0.18
0.2	0.28	0.20	0.17
ICC = 0.2			
0	0.28	**0.22**	0.19
0.1	0.28	0.22	0.19
0.2	0.28	0.21	0.19
ICC = 0.3			
0	0.28	0.23	0.21
0.1	0.28	0.23	0.20
0.2	0.28	0.22	0.20

The significance level is 0.05

The table shows the minimal detectable differences in heart rate (in beats per minute) for 300 homes in each arm for a range of combinations of values of the intracluster correlation coefficient (ICC), the number of individuals per home, and the baseline correlation generated by our stratification

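### The minimal detectable heart-rate difference of 0.22 is in standard-deviation units but is labelled beats per minute, so the stated sensitivity for the primary endpoint is wrong

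*Protocol article*

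**What the plan says.** Under Power calculations, the protocol article cites prior non-randomised studies by which a 3 to 4 °C fall in indoor temperature "should decrease heart rate by several beats per minute". It calls the trial conservatively powered and reports that "the minimal detectable heart rate difference between the cool roof intervention and control condition arm is 0.22 beats per minute", "for 300 homes (in the intent to treat) in both arms", at a 5% significance level and 80% power. It adds: "We further assumed that 15% of homes refuse to participate in the trial and 15% of individuals would be lost to follow-up".

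Table 3 varies the intracluster correlation (ICC: 0.1, 0.2, 0.3), the number of individuals per home (1, 2, 3) and a baseline correlation from stratification (0, 0.1, 0.2). The bold base case is ICC 0.2, two individuals and correlation 0. The entries run from 0.17 to 0.28, and the note reads: "The table shows the minimal detectable differences in heart rate (in beats per minute) for 300 homes in each arm". Neither the section nor the rest of the article gives an SD of heart rate.

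**The concern.** A detectable difference in beats per minute is a multiple of the outcome's SD in beats per minute. Without an SD, the calculation can return only a multiple of the SD. A value of 0.22 is a familiar size for a standardised difference in a trial of this size, and very small for a difference in heart rate.

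What is at stake is how the primary result is read. Set beside an expected effect of several bpm, 0.22 bpm suggests a margin of tenfold or more. A reader would then take a null result as excluding effects down to a fraction of a beat per minute.

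**Working it through.** **Inputs from the article.** Significance level 5% (taken as two-sided; the article does not say) and power 80%. Homes per arm *k*: 300 before losses. Individuals per home *m* = 2 (Sample size: "Each of the 600 households enrolled in the study included one female and one male participant"). ICC = 0.2 and correlation *r* = 0 for the bold cell. Losses of 15% of homes and 15% of individuals. **Not in the article:** the SD, the formula and the effective number of homes.

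**Formula.** Minimal detectable difference = (1.960 + 0.842) × SD × √(2[1 + (m − 1)ICC](1 − r²)/(k m)). For the base case this reduces to 2.802 × SD × √(1.2/k).

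**Step 1: reproduce Table 3.** With SD = 1 and k = 198, the base case is 2.802 × √(1.2/198) = 0.218, printed as 0.22. The zero-correlation rows are:

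| ICC | m = 1 | m = 2 | m = 3 |
|---|---|---|---|
| 0.1 | 0.282 (stated 0.28) | 0.209 (0.21) | 0.178 (0.18) |
| 0.2 | 0.282 (0.28) | 0.218 (0.22) | 0.192 (0.19) |
| 0.3 | 0.282 (0.28) | 0.227 (0.23) | 0.206 (0.21) |

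With the other two correlations included, all 27 cells match to two decimals for k from 197.5 to 199.

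**Step 2: try the stated losses.** 300 × 0.85 × 0.85 = 216.75 homes. Normal quantiles give 0.209 for the base case and match 3 of 27 cells. Quantiles of t on 24 degrees of freedom (25 villages minus 1, a guess at the method) give (2.064 + 0.857) × √(1.2/216.75) = 0.217 and match 23 of 27 cells, or 26 of 27 if the correlation reduces only the within-home variance. SD = 1 is used here too.

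**Step 3: what SD would make 0.22 bpm true?** Only SD/√k enters the formula, so the table cannot separate the two. The homes available bound the answer (normal quantiles):

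| Homes per arm | Difference at SD = 1 | SD needed for 0.22 bpm |
|---|---|---|
| 198 | 0.218 | 1.01 |
| 216.75 | 0.209 | 1.06 |
| 255 (15% of homes lost), 1.7 persons each | 0.203 | 1.08 |
| 255, 2 persons each | 0.192 | 1.14 |
| 300 | 0.177 | 1.24 |

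At an assumed SD of 10 bpm, detecting 0.22 bpm would take 1.2 × (2.802 × 10/0.22)², or about 19,500 analysed homes per arm.

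**Step 4: convert.** 0.22 × SD is 1.8 bpm at SD 8, 2.2 at SD 10 and 3.3 at SD 15. At SD 10, the whole table runs from 1.7 to 2.8 bpm.

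**Step 5: power.** The standard error is SD × √(1.2/k); at SD 10 it is 0.78 bpm with 198 homes and 0.69 with 255.

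| SD (assumed) | Power for 0.22 bpm | Power for 2 bpm | Power for 3 bpm |
|---|---|---|---|
| 8 | 6–7% | 90–95% | over 99% |
| 10 | 6% | 73–83% | 97–99% |
| 15 | 5–6% | 40–49% | 73–83% |

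Each range covers 198 to 255 homes per arm.

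**Step 6: repeated visits.** Averaging *n* visits with within-person correlation ρ multiplies the SD by √((1 + (n − 1)ρ)/n). At SD 10 and 200 homes, 12 to 24 monthly visits with ρ of 0.3 to 0.7 still leave a detectable difference of about 1.2 to 1.9 bpm.

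**The case against.** A condensed article may leave the SD to a fuller document, and heart rate is measured repeatedly, which would shrink the effective SD. The first point excuses the missing SD but not a printed unit that the numbers contradict. The second fails on Step 6, and Table 3 has no repeated-visit input.

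Other objections limit what may be concluded, and they stand:

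- A reader might infer that the table also contradicts the stated losses. That is not shown. The article names neither formula nor degrees of freedom, the t version in Step 2 comes close with 217 homes, and 198 is a fitted value that appears nowhere in the article.
- A reader might put the overstatement at tenfold. That is the assumed SD of 10 restated; the factor is whatever the SD is.
- A reader might infer that the trial is underpowered, or that the detectable difference equals the expected effect. The article expects several bpm without a number. At SD 10, power for 3 bpm is 97% or more; it falls to about 73 to 83% only at SD 15.
- The article ties its claim of conservative powering to uncertainty in earlier findings and the many secondary endpoints, not to 0.22 bpm alone. The claim may survive conversion; it needs checking, not automatic removal.
- Recruitment and data collection are over, and the randomisation and planned analysis do not depend on this figure. This is a correction to reporting and interpretation.

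**Conclusion.** The concern holds as a unit error. The sentence and the Table 3 note label standardised differences as beats per minute. This conclusion does not depend on how losses were handled, because every treatment tried implies an SD of about 1.0 to 1.24 bpm, which is not plausible between adults.

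The size in bpm rests on an SD that the documents do not give. Assuming 10 bpm (8 to 15), the base-case detectable difference is 2.2 bpm (1.8 to 3.3), and power for a true 0.22 bpm is barely above the significance level. The apparent wide margin over the expected effect largely disappears. The documents support a finding of misstated sensitivity for the sole primary endpoint; they do not support a finding of inadequate power for several bpm.

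**What to change.** - Relabel the sentence and Table 3 as differences in SD units.
- State an assumed heart-rate SD with its source, and give the detectable difference in bpm beside it (for illustration, 0.22 SD is 2.2 bpm if the SD is 10).
- State the formula, the quantiles or degrees of freedom, and the effective homes per arm after each 15% loss, so that the table can be reproduced.
- Check the description of the trial as conservatively powered against the value in bpm.
- Interpret any null result against the converted figure and the confidence interval, not against 0.22 bpm.

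The cost is a wording change and one recalculated table. No participants or data are added, and the stated figure becomes less favourable.

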## Methods: assignment of intervention

We stratified households to cool roof intervention or control — first by village and subsequently by roof type (mud brick or tin). After identifying and assigning participants to village and roof type strata, we used a computer algorithm generated by the field team in Nouna to randomize and assign participants to the cool roof intervention or control arm. Therefore, we were able to balance the control and treatment arms by village and roof type covariates. Allocation concealment was ensured through only the site lead in Nouna having encrypted/password-protected access to the household data and the subsequent use of an automated computer-generated algorithm for randomization. Prior to randomization, there was no apriori knowledge of group assignments. The computer-generated allocation sequence used for randomization was not released until households consented to participate in the trial. The site allocation was revealed on March 31, 2021. This is a single-blinded study, where the households are aware of the intervention assignment and all researchers, except for two senior biostatisticians, are unaware of the household group assignments.

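### Table 3's 0.22 beats per minute for 300 homes per arm is printed without a heart-rate SD, and fits the stated homes and losses only if that SD is about 1.05 to 1.23 bpm

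*Protocol article*

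**What the plan says.** All figures come from the protocol article.

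- **Detectable difference.** The Power calculations section says that "the minimal detectable heart rate difference between the cool roof intervention and control condition arm is 0.22 beats per minute", "for 300 homes (in the intent to treat) in both arms, assuming a significance level of 5% and power of 80" per cent. This is the bold cell of Table 3: ICC 0.2, two individuals per home, baseline correlation 0.
- **Table 3 note.** "The table shows the minimal detectable differences in heart rate (in beats per minute) for 300 homes in each arm". The 27 cells cross ICC 0.1, 0.2 and 0.3 with one, two or three individuals per home and baseline correlation 0, 0.1 or 0.2.
- **Losses.** "We further assumed that 15% of homes refuse to participate in the trial and 15% of individuals would be lost to follow-up". The text does not say whether the table includes them.
- **Enrolment.** The Sample size section reports 600 homes randomised 1:1: "Each of the 600 households enrolled in the study included one female and one male participant".
- **Order of consent and allocation.** The section on assignment of intervention says: "The computer-generated allocation sequence used for randomization was not released until households consented to participate in the trial".

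No SD of heart rate appears in the power section, in the endpoint table or anywhere else in the article.

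**The concern.** A detectable difference in beats per minute needs an SD in beats per minute. Without it, the printed figure cannot be tied to the printed number of homes or to the two losses. The table may describe 300 homes per arm, about 217 after both losses, or a smaller number on a standardised scale.

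This is the article's only statement of how small an effect on the primary endpoint the trial can detect. If heart rate shows no difference, readers will use 0.22 bpm to judge how informative that result is. They would then be relying on a figure whose unit, sample and loss allowance are not established, and which could be wrong severalfold if taken literally in bpm.

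**Working it through.** **Inputs.** From the Power calculations section: two-sided 5% (sidedness is not stated, so two-sided is assumed), 80% power, k = 300 homes per arm, m individuals per home, ICC, baseline correlation r, and two losses of 15%. The SD is not given and is treated as unknown.

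**Formula.** MDD = SD × (1.960 + 0.842) × √[ 2 × (1 + (m − 1) × ICC) × (1 − r²) / (k × m) ], compared with all 27 printed cells at two decimals.

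**Step 1: the printed base case at SD = 1.** With m = 2, ICC = 0.2 and r = 0:

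| Homes per arm | Base case (printed 0.22) | Cells matched |
|---|---|---|
| 300 | 2.802 × √(2.4/600) = 0.177 | 0 of 27 |
| 255 (300 × 0.85) | 0.192 | 0 of 27 |
| 216.75 (300 × 0.85 × 0.85) | 0.208 | 3 of 27 |
| 198 and 199 | 0.218 | 27 of 27 |

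With t quantiles in place of normal ones, 199 and 200 homes match all 27.

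**Step 2: free the SD.** The formula depends on SD/√k, so the SD and the number of homes cannot be separated. All 27 cells also match at:

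- 300 homes with SD about 1.23 bpm (1.2275 to 1.233);
- 255 homes with SD about 1.13 bpm;
- 216.75 homes with SD about 1.045 bpm.

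At SD 1.23 the 300-home label holds, but the losses are not in the table: the base case would become 0.189 × 1.23 = 0.23 with individual loss alone, and about 0.25 to 0.26 with both losses. At SD 1.045 both losses are in, but the table then describes about 217 whole homes.

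**Step 3: a check that does not depend on the SD.** If 15% of individuals are lost at random from two-person homes, 0.85² = 0.7225 of homes keep both members and 2 × 0.85 × 0.15 = 0.255 keep one. Entering individual loss this way (and correspondingly for m = 1 and 3) matches at most 24 of 27 cells over 120 to 420 homes at SD = 1, which is equivalent to varying the SD. Using 0.85m people per home matches at most 22. Only whole m = 1, 2, 3 matches all 27. Under this formula, individual loss was therefore either left out or entered as loss of whole homes.

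**Step 4: the enrolled sample.** For 300 homes with random 15% individual loss, the information per arm at ICC 0.2 is 300 × (0.7225 × 2/1.2 + 0.255) = 437.75. The MDD is SD × 2.802 × √(2/437.75) = 0.189 × SD. The range is 0.183 to 0.196 × SD over ICC 0.1 to 0.3.

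| Assumed SD (bpm) | 300 homes, no loss | 300 homes, 15% individual loss |
|---|---|---|
| 5 | 0.89 | 0.95 |
| 10 | 1.77 | 1.89 |
| 15 | 2.66 | 2.84 |

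These SDs are illustrative; the article gives none.

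**The case against.** The strongest defence is that nothing here proves the 300-home label wrong. The SD and the number of homes are confounded, so a reader who sees the exact match at 198 to 200 homes might infer that the table was computed for that number. That match depends on SD = 1, which the article never states. With SD 1.23 the label is exact, and with SD 1.045 both losses fit. This objection stands, and the 199-home figure must be read as conditional.

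The rescuing SDs are nevertheless hard to credit. An SD of 1.23 bpm would put about 95% of normally distributed values within 1.96 × 1.23 = 2.4 bpm of the mean. The same section expects the intervention to lower heart rate by several bpm; taking 3 as an illustration, that would be 3/1.23 = 2.4 SDs.

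On refusal, a reader might infer a flat contradiction between the 15% allowance and the 600 homes enrolled. That goes too far. A planning assumption may differ from what recruitment achieved, and the intention-to-treat remark could point to homes declining the coating after allocation, although the text does not say so. What stands is narrower: refusal to join the trial came before allocation was released, so it does not reduce the 300 homes per arm. The article was submitted after recruitment, when this was known.

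**Conclusion.** The point holds as a defect in a printed figure, with its direction undetermined. The 0.22 bpm for 300 homes per arm can be reconciled with the stated inputs only at an SD of about 1.23 bpm with no losses, or about 1.045 bpm with both losses and about 217 homes.

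On the natural alternative, standardised differences with SD = 1, the unit label and the 300-home label both fail: the base case would be 0.18 for 300 homes, 0.19 with 15% individual loss and 0.21 with both losses.

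A reader might conclude that the table is merely pessimistic, since at SD = 1 power at 0.22 for 300 homes with individual loss is about 90% (88% to 92% over ICC 0.1 to 0.3). The article does not support that, because it labels the values in bpm. At an SD of 5 or more the detectable difference for 300 homes is at least 0.89 bpm, about four times the printed value. Nor does this show that the trial is underpowered: even at an assumed SD of 15, 2.66 to 2.84 bpm may be within the several bpm expected.

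The conclusions rest on the standard cluster formula, a two-sided test and equal arms.

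**What to change.** 1. State the heart-rate SD used, its source, and whether Table 3 is in SD units or beats per minute.
2. Recompute Table 3 for the 300 consented homes per arm with the 15% individual loss and no refusal deduction.
3. Replace 0.22 in the text with the result in the stated unit: about 0.19 if in SD units at ICC 0.2, or 0.189 times the stated SD if in bpm. Writing 0.19 beats per minute without an SD would only repeat the problem.
4. In the table note, give the number of homes and people used and say how each loss enters. If the older planning figures are kept, label them as such, give the number of homes they assume, and say whether refusal meant declining the trial or declining the coating.

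The cost is one closed-form recalculation and edits to a table, its note and the accompanying text. Trial conduct does not change.

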## Methods: assignment of intervention

We stratified households to cool roof intervention or control — first by village and subsequently by roof type (mud brick or tin). After identifying and assigning participants to village and roof type strata, we used a computer algorithm generated by the field team in Nouna to randomize and assign participants to the cool roof intervention or control arm. Therefore, we were able to balance the control and treatment arms by village and roof type covariates. Allocation concealment was ensured through only the site lead in Nouna having encrypted/password-protected access to the household data and the subsequent use of an automated computer-generated algorithm for randomization. Prior to randomization, there was no apriori knowledge of group assignments. The computer-generated allocation sequence used for randomization was not released until households consented to participate in the trial. The site allocation was revealed on March 31, 2021. This is a single-blinded study, where the households are aware of the intervention assignment and all researchers, except for two senior biostatisticians, are unaware of the household group assignments.

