**Fig. 1 Fig1:**
[figure not shown]
Prominent roof types in Nouna, Burkina Faso. **a** Traditional mud brick roof. **b** “modern” tin roof. **c** Thatch roof. Source: Schoeps et al. (2014)

In a previous survey of housing conditions in Nouna, Burkina Faso, we found that average roof surfaces were 18 m^2^ [37]. Most homes in this area use mud bricks or “adobe” roofs coated with a fatty shea butter known as “beurre de Karité”, accounting for 75% of households in 2014 (Fig. 1a). Tin roofs are the second most prevalent, with 20% of house households using them (Fig. 1b), followed by thatch roofs at 4% (Fig. 1c). Tin roofs are increasingly prevalent with rising income and involve less maintenance than mud brick roofs. Both the traditional mud brick and the ‘modern’ tin roofs can be coated with a cool roof coating. Moreover, applying the cool roof coating to traditional mud brick-roofed homes effectively conceals the roofs, given that the roofs possess a slightly raised outer wall measuring 15 cm in height.

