#### Outcomes

Table 2 shows the primary and secondary endpoints, including the definition, functional form of the variable, and measurement approach. Figure 5 shows the schedule of enrollment, intervention, and assessment. The primary outcome is heart rate; we collect three measurements monthly from every participant during monthly home visits. In addition to the primary outcome, we are collecting data to assess the effects of cool roofs on (i) secondary environmental outcomes, including ambient temperature and humidity (measured using iButton sensors), and (ii) secondary health outcomes, such as blood pressure, body temperature, heat-related outcomes, blood glucose, sleep, cognition, mental health, health facility utilization, economic and productivity outcomes, mosquito count, life satisfaction, gender-based violence and food consumption. We randomly selected 152 participants [intervention, *n* = 76 (38 women, 38 men) versus control, *n* = 76 (38 women, 38 men)] to receive a smartwatch that continuously monitors heart rate, sleep, and activity. Between August 2021 and July 2022, our participants used the Withings Pulse HR smartwatch for data collection. In July 2022, owing to the fragility of the Withings Pulse HR, we replaced these devices with the Garmin Vivosmart 5 smartwatch. Several Withings Pulse HR smartwatches were breaking with participant use in the field, necessitating this replacement.

**Table 2 Tab2:** Primary and secondary endpoints of the cRCT

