## Methods: data collection, management, and analysis

### Data collection plan

We are collecting trial data from a variety of sources for measuring health, indoor climate, economic, and behavioral outcomes (Table 2). Our primary outcome — heart rate — is collected monthly by trained field staff using an Omron portable automated sphygmomanometer. We present a complete list of secondary outcomes, including the associated instruments used for data collection in Table 2. Additionally, we are collecting continuous health indicators, including heart rate, sleep, and activity using a Withings Pulse HR or Garmin Vivosmart 5 smartwatch worn by a subset of participants.

We are collecting HbA1C blood samples - an indicator of long-term glucose control as two-panel measurements in the hottest months of 2021 and 2022, respectively, using the HemoCue® HbA1c 501 System. A qualified phlebotomist took 4 ml of whole blood by venipuncture for each participant. The phlebotomist labeled the collection tube with the participant's first and last name, and their household, individual and study identifying codes. Blood samples collected in different villages were stored in a refrigerator, and transfered to the laboratory within 48 h. Our laboratory technicians verified that HbA1c samples matched participants and recorded measurements systematically on examination forms according to protocols supplied by HemoCue®. Blood samples were subsequently disposed of in accordance with the laboratory's biological waste disposal procedure. We removed all identifiable information, except the individual identification code, prior to conducting data analysis.

We are collecting indoor temperature and humidity data using the DS1923-F5 iButton hygrochron temperature and humidity sensors. We are also conducting three independent sub-studies using the cool roof trial infrastructure that will be reported separately. First, we will investigate the effects of cool roofs on mosquito abundance, where light traps and aspirators are deployed during the rainy season to collect mosquito samples from a subset of households. Second, we will investigate the effects of cool roofs on farmer productivity, where GPS devices will record individual movement and remote sensing will provide data on crop harvest yield. Finally, we will investigate the effects of cool roofs on food consumption, psychosocial well-being, and gender-based violence from data collected during monthly home visits.

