## Methods: monitoring

We have appointed an independent steering committee comprising three members: a climate change and health domain expert, a clinical trials expert, and a biostatistician to maintain project oversight throughout the study. The steering committee will convene three meetings, the last of which will be in June 2023. At these meetings, the research team will review the conduct of the trial, including a review of adherence to intervention components, logistical issues, and completeness and quality of collected data. Our biostatisticians will also present emerging effect estimates in the intervention and control arms to the steering committee, who will ascertain whether the results display:Null finding(s) > indicating the study should stopSignificant finding(s) > indicating the study should stopEmerging positive finding(s), but statistically insignificant > indicating the study should potentially continue, and therefore, the data collection should continue for a recommended duration.

The cool roof is a passive home cooling intervention and, therefore, required no human interaction or behavior change on behalf of our participants. We conducted an education program through our field staff to ensure study participants did not place items on their roofs that could obstruct the optimal performance of the cool roof. Our field teams regularly monitored roofs during monthly home visits and highlighted any deterioration or other issues for resolution. Throughout the trial, our study team exchanged regular communication via virtual and phone calls, emails, and short messages about trial progress.

We encountered, however, adherence issues with participants removing smartwatches, particularly at night. Our field team explained the importance of smartwatch data and encouraged non-compliant individuals to wear the device during home visits.

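### The masking statement exempts only two biostatisticians, but it cannot hold for field staff who collect outcomes at the home visits where roofs are inspected

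*Protocol article*

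**What the plan says.** Under Methods: assignment of intervention, the protocol article sets the level of masking in one sentence. It begins "This is a single-blinded study, where the households are aware of the intervention assignment" and goes on to say that "all researchers, except for two senior biostatisticians, are unaware of the household group assignments". No other role is singled out.

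Other sections describe what happens at the homes:

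- **Outcomes**, on heart rate: "we collect three measurements monthly from every participant during monthly home visits".
- **Data collection plan**, on who takes it: heart rate "is collected monthly by trained field staff using an Omron portable automated sphygmomanometer". The abstract says the monthly visits serve both objective and subjective outcomes, and the Discussion says local interviewers were trained for them.
- **Methods: monitoring**, on the roofs: "Our field teams regularly monitored roofs during monthly home visits and highlighted any deterioration or other issues for resolution". The same section adds: "We conducted an education program through our field staff to ensure study participants did not place items on their roofs".
- **Consent and withdrawal**: damage to the coatings will be repaired while the study runs.
- **Intervention**: the control condition is no cool roof application.
- **Housing features in Nouna**: on mud-brick roofs, which have a raised outer wall of 15 cm, applying the coating "effectively conceals the roofs". Nothing similar is said for tin roofs.

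**The concern.** Households know their arm, so the only masking that the single-blind label can refer to is that of the researchers. A reader will take the sentence to include the people who record the outcomes, because only two biostatisticians are excepted. The procedures at the homes do not support that reading.

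The stake is how much weight the interview endpoints can bear. If both the respondent and the interviewer know the arm, expectations on either side can move answers on heat strain, mood, sleep or life satisfaction with no physiological change behind them. A reader who believes the interviewer was masked will discount that possibility more than is justified. A later SAP would not cure this, because the article makes a positive statement about masking that its own procedures do not bear out.

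**Working it through.** The masking statement carries no figure to reproduce. The check is whether it is consistent with the described procedures, followed by a count of the endpoints exposed.

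**1. Can a field assessor remain unaware of the arm?**

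- Outcomes are taken by field staff at monthly home visits (Outcomes; Data collection plan).
- Roofs are inspected by field teams at monthly home visits, and deterioration is flagged (Methods: monitoring). Repairing the coating requires someone to have noticed the damage (Consent and withdrawal).
- One arm has a coating and the other has none (Intervention), so looking at the roof reveals the arm.
- The person being interviewed knows the arm (Methods: assignment of intervention) and can reveal it.
- No section describes separate assessors kept away from the roofs, or any instruction to respondents not to disclose their arm.

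Either route, the roof or the respondent, is enough to unmask the person recording the outcome.

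**2. Does the concealment of mud-brick roofs rescue the statement?**

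From Sample size, there are 25 villages with 12 mud-brick and 12 tin homes each:

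- mud brick: 25 × 12 = 300 homes
- tin: 25 × 12 = 300 homes
- total: 600

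Concealment is therefore described for 300 / 600 = 50% of homes. Even there it can work only for someone who does not look at the roof itself. It does nothing about disclosure by the household.

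**3. Which endpoints are exposed?**

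Table 2 lists 22 secondary endpoints. Those whose measurement is wholly or partly an answer from the participant or a household proxy are:

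1. indoor thermal comfort (heat strain questions)
2. dehydration (urine chart plus a question)
3. sleep (recall, plus smartwatch in a subset)
4. depression
5. aggression
6. clinic utilization
7. hospitalization
8. children's educational attainment (proxy)
9. household consumption expenditures (proxy)
10. life satisfaction
11. food consumption score

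That is 11 / 22 = 50%. Dehydration and sleep are partly self-reported and the other nine wholly so. Gender-based violence is named as an outcome in the text but has no row in Table 2, so it is outside the count.

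**4. Which endpoints are little exposed?**

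Heart rate and blood pressure come from an automated device. Temperature and humidity come from data loggers, and HbA1c from a laboratory analyzer. The assessor has little influence on any of these readings.

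**The case against.** The strongest reply is that the sentence speaks of researchers, not outcome assessors. The article usually calls the people at the homes field staff, field teams or local interviewers, and Data management lists those with database access as investigators, biostatisticians and data scientists. If researchers means that off-site group, the masking statement and the roof inspections can both be true. This reply stands in part: a reader might infer that no masking existed anywhere, and the documents do not show that. But the term is not defined, and Eligibility for homes uses research team in connection with safety at the homes. On the narrow reading, the article simply says nothing about masking of the people who record outcomes, while leaving readers to suppose that it does.

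Second, nowhere is it stated that the same individuals take outcomes and inspect roofs, and several field groups are mentioned. This is fair: that they are the same people is a likely inference. The point does not rest on it alone, because respondents who know their arm are interviewed by the assessors.

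Third, households' knowledge is already disclosed, and no masked option for them is described. That is correct. How much bias an unmasked interviewer adds to answers from an unmasked respondent cannot be derived from the article. The count of 11 measures exposure, not bias.

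Three further inferences are tempting and not supported:

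- **Committee reporting.** Methods: monitoring says: "Our biostatisticians will also present emerging effect estimates in the intervention and control arms to the steering committee". A reader might see this as breaking the mask. Estimates by arm do not reveal any household's allocation, and the article does not say that the wider team sees them.
- **Unmasked analysts.** The two biostatisticians are openly named as exceptions. The article does not say that they do the cleaning or choose covariates, and the exploratory wording under Statistical analysis concerns imputation of missing covariates only.
- **Mud brick against tin as a test of bias.** Households know their arm under both roof types. The smartwatch analysis section also anticipates variation by roof type for thermal reasons, so a difference could be a true one.

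**Conclusion.** The point holds for field outcome assessors. The masking statement, read as written, is not compatible with the procedures described at the home visits, and no arrangement for masked assessors is given. It does not follow that off-site researchers were unmasked.

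The exposure is 11 of 22 secondary endpoints. The primary endpoint, heart rate read by an automated device, is little affected, so this does not threaten the main comparison. It is a correction that should be made because it changes what the self-reported endpoints can support.

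The conclusion assumes that the people collecting outcomes either see the roof or learn the arm from the household, and that no separate masked assessors existed. Documentation of such assessors would remove the concern about the interviewer, but not about the respondent.

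**What to change.** - Reconcile Methods: assignment of intervention with Methods: monitoring by stating masking for each role: households, field assessors, site lead, laboratory, data managers and analysts.
- Describe households and field assessors as unmasked, unless separate masked assessors can be documented.
- In the results report, label the 11 self- or proxy-reported secondary endpoints as unmasked, and do not let any of them stand as the sole support for a claim of benefit.

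Trial status says data collection ended on June 30, 2023, so assessor masking cannot now be added and the remedy lies in reporting. Analysis on scrambled arm labels by the two biostatisticians is not requested, because they already know the allocation. The cost is a few sentences of text. The downside is a weaker, but accurate, masking claim.
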